**Figure 1 figure1:**
[figure not shown]
Photographs of the neonatal characteristics for the tablet app for the simplified gestational age scoring system (T-SGAS).

**Table 1 table1:** Conversion of the tablet app for the simplified gestational age scoring system (T-SGAS) to gestational age categories [13].

T-SGAS total score	Gestational age (weeks)
<7	<32
7-9	≥32 to <35
10-13	≥35 to <37
>14	≥37

### Study Design for the T-SGAS Validation Study

The study is a multicenter evaluation of the T-SGAS that will be conducted in three second level care birthing facilities in and around Nagpur, India (Daga Memorial Hospital, Nagpur; Government Hospital, Bhandara; and Government Hospital, Wardha), where most of the deliveries are conducted by ANMs. Each facility will have a team of ANMs and data collectors trained to use the T-SGAS. Over the study period, two ANMs will be available at all times to independently use the T-SGAS to calculate the newborn’s GA within 24 hours of birth. Since the ANMs will be blinded to the neonates actual GA, the data collector will obtain the actual GA data by assessing the mother and her chart, to ascertain her neonate’s eligibility for analysis. This will be done after the ANMs have assessed all neonates whose mother has consented to her newborn participating in the study.

### Eligibility Criteria for the Newborns

During 12-hour study shifts, all mothers who meet the inclusion criteria and have no exclusion criteria (Textbox 1) will be informed about the study and invited to participate. Exclusion criteria were determined on the basis of conditions that could interfere with the assessment of the neonate’s posture. Mothers who are willing to participate will complete a consent process and sign the consent form.

Since it is frequently not possible to obtain and confirm the estimated GA by ultrasound, we decided *a priori* to have additional exclusion criteria for analysis eligibility, to improve the likely validity of the GA estimated by ultrasound, as follows:

Women whose estimated GA from the date of the LMP is not within 1 week of the GA estimated from the ultrasound;Neonates with GA at birth <20 weeks or >44 weeks based on either the date of the LMP or ultrasound;Two independent assessments of the newborn were not available within the first 24 hours of life; andANMs who had not assessed at least 100 newborns during the study were unavailable.

### Ethics and Consenting

The protocol and the informed consent documents were submitted and approved by the Institutional Review Boards (IRBs) and ethics committees of the Lata Medical Research Foundation IRB (FWA00012971), the Partners Human Research Committee, Boston, MA, and the Boston University Medical Campus IRB. This study is supported by The Eunice Kennedy Shriver NICHD’s Global Network for Women’s and Children’s Health Research. The study was registered on ClinicalTrials.gov (NCT02408783).

### Study Variables

Study variables include the date and time of the neonate’s delivery, delivery outcome, gender, birth weight, and maternal demographic data, including level of maternal education (none, primary, secondary, postsecondary), mode of delivery (vaginal, cesarean section, vaginal assisted), birth weight (grams), date of her LMP, and GA per the hospital-based ultrasound report.

### Implementation of the Study Protocol

Three senior neonatologists with experience in GA assessment at birth and an obstetrician (master trainers) will train the ANMs on the use of the T-SGAS. The training will consist of 4 days of classroom teaching sessions, which include training on Good Clinical Practice guidelines, how to examine the newborn, the different aspects of the 4 physical characteristics of the newborn at different GA, and how to use the T-SGAS. The ANMs will be trained in 3 batches and a final one-day re-orientation training for all ANMs will be conducted prior to the start of the study. The ANMs will then participate in a two-week practical training in the study hospitals. The first week of practical training will be conducted in the delivery room, postnatal wards, and in the special care neonatal units. Training includes adherence to asepsis protocols of the nursery, as well as one-on-one training of how to use the T-SGAS for assessing singleton live births, conducted by the master trainers. The second week, the trainees will independently assess 30 newborns of varying GA before these babies are independently reassessed by the master trainer. ANMs whose scores for each item agree with the master trainer’s score at least 80% of the time will be considered successfully trained.

The tablet-based forms are password protected and accessible only by using log-in credentials. After log-in, a Case Management Screen appears with the list of facilities and a preinstalled drop-down menu of identification numbers (IDs). The first ANM (ANM-1) sequentially allocates the IDs to the women who consented and delivered singleton live births. ANM-1 evaluates the newborn and uses her log-in credentials to open the electronic study form (SGAS01) that records date and time of delivery, gender of neonate, consent status, and then uses the touch screen to choose pictures that most accurately represent the neonate’s skin, breasts, genitals, and posture (Figure 2). The GA score is then auto-calculated and the neonate is classified into a specific GA group. On completion of the form, a pop-up warning message appears on the screen to verify the assessment and form entries. When verified, the form is saved and cannot be reopened by ANM-1. Completion of the form enables automatic population of subsequent forms with the same ID for the same participant. Color coding is used to identify the pending forms, so that ANM-2 can assess the same newborn using her log-in credentials within 24 hours of birth (using form SGAS02).

Inclusion and exclusion criteria to participate in the tablet app for the simplified gestational age scoring system (T-SGAS) study.Inclusion criteriaMother had regular menstrual cycles prior to pregnancyMother knew the date of her last menstrual periodMother has a report of at least one prenatal ultrasound assessment of gestational age during pregnancy (ideally in the first trimester)Mother and baby are clinically stableMother delivered singleton neonate at the study hospitalNeonate is within the first 24 hours of lifeExclusion criteriaNeonates with birth asphyxia or who were resuscitatedNeonates with major congenital anomalies or signs of neurological depression

Data collectors are senior nurses trained to abstract study data from the hospital records. After ANM-1 and ANM-2 have completed their assessments, the data collector logs in to add the GA from the ultrasound report and the date of the LMP on form SGAS03. This procedure ensures that GA assessment by the T-SGAS is done by the ANMs who do not know the baby’s estimated GA at birth. Additional demographic details of the mother and the newborn, foot length of the newborn, and birth weight are included in this form. These data are used to determine final eligibility for analysis (Figure 3).

Periodic 2-day retraining will be provided to the ANMs and their assessments will have to meet the standard of 80% agreement of items with that of the master trainers. Focus group discussions for the master trainers and ANMs will be conducted to understand the limitations, challenges, and ease of use of the T-SGAS.

**Figure 2 figure2:**
[figure not shown]
Tablet screens showing use of the tablet app for the simplified gestational age scoring system (T-SGAS).

**Figure 3 figure3:**
[figure not shown]
Overview of the T-SGAS study. ANM: auxiliary nurse midwife, GA: gestational age, T-SGAS: tablet app for the simplified gestational age scoring system, LMP: last menstrual period.

#### Quality Control Procedures

The master trainers will complete a GA assessment for 5% of the newborns selected at random to monitor accuracy of the ANMs’ assessment of GA. These data will be entered on form SGAS04. Since the ultrasounds are done for clinical purposes and may not be available at the hospital where the baby is delivered, there are no additional quality control procedures for estimation of GA from the ultrasound. If there is more than one ultrasound available, the earliest ultrasound in the pregnancy will be selected for the GA estimate, ideally one that has been conducted within the first trimester. The accuracy of the ultrasound will likely be improved by requiring the GA by ultrasound to be within 1 week of the mother’s assessment of GA based on her LMP. Form SGAS05 will be used to record any protocol deviations or unexpected events in the course of the neonate’s enrollment.

Data collection and transmission will be on a real time basis to an RTI International Server (Data Coordinating Center), which will allow daily viewing of data by data managers and statisticians. Edit reports (missing data, pending forms, inconsistencies between the forms and data) will be generated on a daily basis and sent to the birthing facilities so that the data collector can verify the data and resolve inconsistencies.

Monitoring will also be conducted by the research staff and master trainers during regular planned and unplanned visits to facilities to review ANM performance.

### Analysis

#### Sample Size

We have assumed that the prevalence of preterm births will be approximately 10% in this population. In a 2-sided test for sensitivity, a sample size of 7440 will achieve 80% power at a significance level of 0.05 when the sensitivity under the null hypothesis is 0.60 and the sensitivity under the alternative hypothesis is 0.65. This sample size will also be sufficient to achieve 80% power at a 0.05 significance level in a 2-sided test for specificity, when the specificity under the null hypothesis is 0.70 and the specificity under the alternative hypothesis is 0.75, which requires a minimum of 704 subjects.

#### Analysis plan

Firstly, we will use the Fleiss kappa statistic to estimate agreement between GA (as a dichotomous outcome) measured by ANM-1 and ANM-2. Since our goal is to evaluate the use of the T-SGAS by ANMs, we will not determine which AMN is “correct” (eg, by having a third AMN independently assess the GA of the baby to resolve disagreement). Instead, we will assess the screening accuracy (sensitivity, specificity, prevalence of preterm) of the T-SGAS for both ANMs using 4 different reference standards: LMP alone, ultrasound alone, either LMP or ultrasound, and both LMP and ultrasound (when GA by ultrasound is within 1 week of the GA estimated by the date of the LMP) [19]. We will also determine the predictive accuracy using the area under a receiver operator curve, based on predicted probability estimates obtained from logistic regression. We will determine from the data the optimal cutoff for the dichotomization of the T-SGAS using tree analysis. For this analysis, each of the four aforementioned reference standards will be separately considered as dependent variables and the birth weight and the T-SGAS as independent variables.

Secondly, we will use latent class analyses [20-23] to predict a preterm birth when neither the GA based on the date of the LMP nor GA based on the ultrasound are treated as a reference standard. Finally, we will conduct classification and regression tree (CART) analyses to identify specific items from the T-SGAS and combine them with birth weight to achieve an improved prediction of a preterm birth, since birth weights are universally measured in health facilities soon after birth. The CART analyses will also provide an optimum protocol for implementation of the T-SGAS in community settings, since birth weights are now universally measured in the health facilities soon after birth. Improvement in discrimination and reclassification using the T-SGAS over the traditional method that uses birth weight and LMP will be quantified using the integrated discrimination improvement index and the net reclassification index, respectively [24,25].

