## Methods

### Development of the Tablet App for the SGAS (T-SGAS)

The development of the T-SGAS was achieved through the following steps: (1) collection of a repository of photographs of the items in the SGAS for preterm and term newborns; (2) selection of photographs for the range of scores for skin, breasts, and genitalia and consensus of neonatology experts for the best photograph of each item score; and (3) development of the Android T-SGAS for visually matching the newborn to the photographs, which auto-calculates the total SGAS and assigns a GA after the user choses the appropriate photograph. A score of <14 is considered to represent preterm, as we had found in our prior study [13].

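### The T-SGAS cut-off is to be re-derived from the validation newborns by a tree that also contains birth weight, and the powered tests are never tied to the prespecified <14 rule

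*Protocol article*

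**What the plan says.** Four statements in the protocol article bear on the cut-off.

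- **Development of the Tablet App for the SGAS (T-SGAS):** "A score of <14 is considered to represent preterm". The value comes from the authors' earlier study, which the Introduction puts at 171 newborns, and the app classifies from the total score.
- **Sample Size:** "In a 2-sided test for sensitivity, a sample size of 7440 will achieve 80% power at a significance level of 0.05", with the hypotheses given as "the sensitivity under the null hypothesis is 0.60 and the sensitivity under the alternative hypothesis is 0.65". Specificity is treated likewise (0.70 against 0.75, minimum 704). No cut-off is named.
- **Analysis plan, cut-off step:** after planning kappa and then sensitivity and specificity for both ANMs, again without a cut-off, it states "We will determine from the data the optimal cutoff for the dichotomization of the T-SGAS using tree analysis". For this analysis each of four reference standards is a separate dependent variable, with "the birth weight and the T-SGAS as independent variables".
- **Analysis plan, CART step:** a further tree combines individual T-SGAS items with birth weight, and "The CART analyses will also provide an optimum protocol for implementation of the T-SGAS in community settings".

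The Objective in the Abstract asks whether the score predicts prematurity on its own and also whether it adds to birth weight. Those are two separate questions.

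**The concern.** The study is presented as a validation of an existing score with an existing cut-off. The plan contains two ways to dichotomise that score, <14 and whatever the tree returns, and does not say which one the powered tests use.

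The tree is also not built to answer the stand-alone question. With birth weight in the model, a T-SGAS threshold may apply only to newborns on one side of a birth-weight split. Running it against four reference standards can give four thresholds. A reader who wants to know whether 14 is the right cut-off for T-SGAS alone would not necessarily get an answer.

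At stake is how a favourable result is interpreted. A higher sensitivity obtained by moving the threshold, at the expense of specificity, could be presented as confirmation of the score as it stands in the app. The CART rule, fitted to the same newborns, could likewise be taken as ready for community use.

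**Working it through.** **1. Reproduce the planned sample size.**

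Inputs from Sample Size: prevalence 10% ("We have assumed that the prevalence of preterm births will be approximately 10% in this population"), two-sided alpha 0.05, power 80%, sensitivity 0.60 against 0.65, specificity 0.70 against 0.75.

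One-sample formula: n = [z(0.975)·√(p0·q0) + z(0.80)·√(p1·q1)]² / (p1 − p0)²

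- Sensitivity: [1.96·√0.24 + 0.8416·√0.2275]² / 0.0025 = (0.9602 + 0.4014)² / 0.0025 = 741.6, so 742 preterm. 742/0.10 = 7420.
- Sensitivity, exact binomial with 0.025 per tail: 744 preterm, reject at 473 or more, power 80.4%. 744/0.10 = 7440, the planned figure.
- Specificity: [1.96·√0.21 + 0.8416·√0.1875]² / 0.0025 = (0.8982 + 0.3644)² / 0.0025 = 637.7, so 638 term. 638/0.90 = 709.
- Specificity, exact binomial: 80% is first reached at 633 term. 633/0.90 = 703.3, so 704, the planned figure.

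Both figures belong to a one-sample test of a single binary rule fixed in advance. Nothing in them allows for choosing the rule from the data.

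**2. What the tree can return.**

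A tree on birth weight and T-SGAS picks whichever split helps most at each node. If it splits on birth weight first, each later T-SGAS threshold is conditional on a birth-weight range. There may then be no T-SGAS threshold, one, or a different one in each branch, and the exercise is repeated for four reference standards. This follows from the stated method and needs no simulation.

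**3. How much one point on the score matters.**

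The documents give no score distribution. Assume an integer score from rounded normals with SD 2.5 in both groups, with <14 placed at the null (sensitivity 0.60) and specificity 0.70. Rounding puts the boundary for <14 at 13.5 and for <15 at 14.5.

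- Sensitivity at <15: z(0.60) = 0.253, plus 1/2.5 = 0.400, gives Φ(0.653) = 0.74.
- Specificity at <15: z(0.70) = 0.524, minus 0.400, gives Φ(0.124) = 0.55.

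One point moves sensitivity by 14 points and specificity by 15, against a planned difference of 5.

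**4. What happens if the sensitivity test is run at a data-chosen cut-off.**

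Simulation with 744 preterm and 6696 term newborns, the cut-off chosen by maximum Youden index (a stand-in for the tree), and true sensitivity of <14 equal to 0.60. The entries are the share of simulated trials that reject 0.60 upwards.

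| Cut-off used | True specificity of <14 | Assumed SD | Rejection |
|---|---|---|---|
| Fixed <14 | 0.60 to 0.75 | 2 to 4 | about 2.5% |
| Data-chosen | 0.70 | 2 / 2.5 / 3 / 4 | 18% / 32% / 43% / 53% |
| Data-chosen | 0.60 | 2.5 | 14% |
| Data-chosen | 0.60 to 0.75 | 2 to 4 | about 8% to 77% (full range) |

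**5. Why it happens.**

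At SD 2.5 and specificity 0.70, 894 of 3000 simulated trials (30%) chose a cut-off other than <14, nearly always <15. Counting only rejections where the chosen rule's own true sensitivity is 0.60 or less, the rate is 1.6% to 2.9%. Mean optimism in sensitivity is 0.3 to 0.7 points. The excess is therefore almost all due to the rule changing, not to overfitting.

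**The case against.** The strongest reply is that the powered tests are already at <14. The app classifies from the total score, ANM-1 cannot reopen a saved form, and the Analysis plan puts kappa on dichotomous GA and the sensitivity and specificity assessment before the cut-off step. On that order the dichotomy is the app's own, and the tree is a later exploration. This largely stands. A reader might infer that the powered tests do not validate the <14 rule, but the documents do not support that: nothing says the tests use the derived cut-off, and at <14 they are a sound external test with the stated power. What remains is that the document never says so and then introduces a second dichotomy.

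A reader might also infer that the 0.05 level fails at a data-chosen cut-off. Step 5 shows no inflation against the chosen rule's own sensitivity. The test would be answering a question about a different rule.

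Birth weight in a tree does serve a stated aim, incremental prediction. That is fair for that aim, but it does not supply a cut-off for T-SGAS alone.

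Finally, the article mentions no cross-validation or optimism correction. The full protocol and SAP are not shown and may contain it, so its absence here is not counted as an error. Nor is any figure for optimism in the CART rule claimed, because it would rest on item and birth-weight distributions that the documents do not give.

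**Conclusion.** The point holds as a defect in how the cut-off is specified, not as a failure of the powered design. Two parts follow from the text alone: the powered tests are not explicitly tied to <14, and the cut-off tree includes birth weight and four reference standards, so it need not yield a single stand-alone threshold. The second part takes the sentence listing the predictors as describing the cut-off tree, which is its natural reading.

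The size applies only if the tests were read at a derived cut-off: rejection of 0.60 in about 8% to 77% of trials when <14 truly has sensitivity 0.60, against about 2.5% at fixed <14. That range rests on an integer binormal score, SD 2 to 4, specificity 0.60 to 0.75 and the Youden index in place of the tree. The direction is the same throughout, but no single value in the range should be quoted as the effect. The sample size of 7440 is unaffected.

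**What to change.** 1. State in Sample Size and Analysis plan that the powered sensitivity and specificity tests use the prespecified <14 rule. Table 1 lists 10-13 and >14, which leaves a score of exactly 14 without a category, so reconcile it with the <14 wording at the same time.
2. Derive any new cut-off from T-SGAS alone, as a secondary, exploratory analysis.
3. Keep the tree with birth weight for the question of what T-SGAS adds to birth weight.
4. Label the derived cut-off and the CART implementation rule as development results. Report their accuracy with cross-validation or bootstrap optimism correction, repeating the selection in each resample, unless the SAP already does so.

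The cost is a few sentences and some computing time, with no new data and no change in sample size. The reported accuracy of the derived rules will be slightly lower.

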**Objective:**

The objective of this study is to adapt the scoring system as a tablet app (potentially scalable approach) to assess feasibility of use and to validate whether the scoring system accurately predicts prematurity by itself, over and above birth weight in a large sample of newborns.

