The objective of this paper is to describe the development of the T-SGAS, its preliminary assessment of feasibility, and a protocol to evaluate whether it accurately predicts prematurity in a large sample of newborns. The programmatic feasibility of using the app will be evaluated by assessing the agreement of GA assessments performed by 2 ANMs. The accuracy of the app will be assessed by comparing the assessment of preterm vs term-based newborns on LMP alone, ultrasound alone, and the combination of LMP and ultrasound.

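### No stated analysis compares T-SGAS with birth weight alone, although the Objective asks whether it predicts prematurity over and above birth weight

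*Protocol article*

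**What the plan says.** The Objective in the abstract is to "validate whether the scoring system accurately predicts prematurity by itself, over and above birth weight in a large sample of newborns". This contains two questions: how accurate the score is alone, and what it adds once birth weight is known. The Introduction restates the aim more narrowly, as "a protocol to evaluate whether it accurately predicts prematurity in a large sample of newborns", without birth weight.

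Sample Size rests on one-sample tests. It assumes 10% preterm prevalence and says: "In a 2-sided test for sensitivity, a sample size of 7440 will achieve 80% power at a significance level of 0.05", where "the sensitivity under the null hypothesis is 0.60 and the sensitivity under the alternative hypothesis is 0.65". A parallel test of specificity, 0.70 against 0.75, is said to need at least 704 subjects.

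Analysis plan describes:

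- sensitivity and specificity of T-SGAS for each ANM against four reference standards (LMP, ultrasound, either, both);
- "predictive accuracy using the area under a receiver operator curve, based on predicted probability estimates obtained from logistic regression";
- a tree to choose the T-SGAS cutoff, followed by the statement that "each of the four aforementioned reference standards will be separately considered as dependent variables and the birth weight and the T-SGAS as independent variables";
- CART combining T-SGAS items with birth weight;
- IDI and NRI for T-SGAS, with birth weight plus LMP as the base.

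The same section notes that birth weight is measured universally in health facilities.

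**The concern.** Where every newborn is already weighed, the app is worth deploying for the increment question only if it separates preterm from term better than the scale does. The matching null is that T-SGAS carries no information about preterm status once birth weight is known. None of the listed analyses has that null or estimates the gain over birth weight by itself. A reader could see a rejected null for sensitivity and a high AUC, and take both as support for the second half of the Objective. A score that merely tracks infant size could produce the same results.

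**Working it through.** **1. The plan's own figures.** Inputs from Sample Size: two-sided alpha 0.05, power 0.80, prevalence 0.10.

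n = [z(0.975)·√(p0(1−p0)) + z(0.80)·√(p1(1−p1))]² / (p1−p0)²

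- Sensitivity, 0.60 vs 0.65: (1.960·0.4899 + 0.842·0.4770)² / 0.0025 = 742 preterm, so 742/0.10 = 7420. The exact binomial gives 744 preterm (power 0.804), so 744/0.10 = 7440, as stated.
- Specificity, 0.70 vs 0.75: (1.960·0.4583 + 0.842·0.4330)² / 0.0025 = 638 term, so 638/0.90 = 709. The exact binomial gives 633 term (power 0.803), so 633/0.90 = 703.3, rounded up to 704, as stated.

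Both sizes are right for the tests described. Birth weight enters neither.

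**2. Comparator used by each analysis.**

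| Analysis | Compared with | Gain over birth weight alone? |
|---|---|---|
| Sized tests | constants 0.60 and 0.70 | No |
| Logistic AUC, predictors joint | nothing named | No |
| Logistic AUC, T-SGAS only | nothing named | No |
| CART with birth weight | no weight-only tree named | No |
| IDI / NRI | birth weight + LMP | No, different base |

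**3. Illustration with zero true gain.** The documents give no accuracy for birth weight, so it is assumed. Each run has N = 7440 and 10% preterm. Birth weight is standard normal with its mean lowered by d in preterm infants. T-SGAS is birth weight plus independent noise, scaled so that its own separation is 1.15; given birth weight it says nothing about preterm status. At a cutoff of −0.72 its true sensitivity is about 0.67 and its specificity about 0.76. There were 300 runs per row.

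| d (birth weight) | AUC, weight only | AUC, weight + T-SGAS | Sensitivity test vs 0.60 rejects | T-SGAS coefficient given weight, p < 0.05 |
|---|---|---|---|---|
| 1.3 | 0.8209 | 0.8210 | 95.0% | 3.0% |
| 1.5 | 0.8552 | 0.8553 | 96.3% | 3.3% |
| 2.0 | 0.9213 | 0.9214 | 96.7% | 3.3% |

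The mean IDI over birth weight was about 0.0002 in each row. The 95% to 97% is power: sensitivity really does exceed 0.60 in this set-up, so rejection is correct. The sized test and the joint AUC are simply silent on the increment, whereas the conditional test addresses it.

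**4. Does the IDI with LMP in its base fill the gap?** LMP defines, wholly or partly, the standards LMP alone, either, and both. Assume a gestational age SD of 1.6 weeks, a dating error SD of 1 week for LMP and for ultrasound, and a T-SGAS that is informative beyond birth weight. Two simulated data sets of 7440 gave:

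| Reference standard | IDI over birth weight | IDI over birth weight + LMP |
|---|---|---|
| LMP | 0.118, 0.104 | 0.000, 0.000 |
| Ultrasound | 0.129, 0.118 | 0.035, 0.032 |
| Either | 0.140, 0.123 | 0.011, 0.008 |
| Both, within 1 week | 0.157, 0.143 | 0.003, 0.003 |

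With LMP as both predictor and part of the outcome, little is left for T-SGAS to explain even when it helps. The simulated preterm fraction ran from 9% to 21% across standards, and the one-week restriction was applied only to the last row, so the sizes are indicative.

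**The case against.** The strongest reply is that the plan does contain an added-value analysis. IDI and NRI are incremental measures, so a reader who inferred that added value is ignored altogether would be wrong. That stands. What remains is that their base includes LMP, which is not the comparator in the Objective and overlaps with three of the four outcomes.

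A reader might also infer that the AUC definitely pools the two predictors. The text does not settle this: the sentence naming them follows the one about the cutoff tree and may refer only to the tree. If so, the AUC may be for T-SGAS alone, which still shows no gain over birth weight. If the logistic model is joint, its T-SGAS coefficient would answer the increment question, but the article does not say that it will be tested or reported.

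A third tempting reading sets the high rejection rates against a nominal 5% and calls them inflated type I error. They are not: the nulls in Sample Size are false in that simulation. Nor is the sample size wrong, and sizing a study on one of two questions is legitimate, especially as the Introduction states only the accuracy question.

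CART can leave out uninformative items, so the lack of a weight-only tree is a lesser matter. Finally, model detail often belongs in an SAP, which is not shown and may add this comparison. The point does not rest on missing detail, however: the article itself names its incremental base, and that base does not match its Objective.

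**Conclusion.** The concern holds in a limited form. The Objective poses an increment question against birth weight, and no analysis stated in Sample Size or Analysis plan answers it. The sized tests are correct for stand-alone accuracy. The AUC, whichever predictors it uses, has no weight-only counterpart. IDI and NRI measure gain over a different base.

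The mismatch of comparators follows from the text and needs no assumption. The simulated sizes (joint and weight-only AUC within 0.0002; IDI of 0.10 to 0.16 over birth weight falling to between 0.00 and about 0.03 once LMP is in the base) rest on assumed birth-weight accuracy and dating error. They illustrate the mechanism and do not predict this study's results. This should be corrected in the analysis; it does not undermine the sample size or the accuracy analysis.

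**What to change.** In Analysis plan, for each of the four reference standards and on the same newborns, fit three logistic models: T-SGAS alone, birth weight alone (continuous), and both. Then:

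- report the three AUCs, using T-SGAS alone for the stand-alone question;
- for the increment, report the likelihood-ratio test for T-SGAS given birth weight and the paired AUC difference (both minus birth weight alone) with its 95% CI;
- report IDI and NRI against the birth-weight-only base as well as the planned one;
- say which analysis the sentence naming the predictors refers to.

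In Sample Size, state that 7440 and 704 support only the stand-alone question. A weight-only tree beside the CART is optional.

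The cost is some wording and about two extra model fits per reference standard. Birth weight is already recorded on form SGAS03, so no new data are needed. The small downside is that the reported gain may look less favourable than a joint AUC.
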